## Abstract

**Background:**

Huntington’s disease is a progressive, neurodegenerative disease with autosomal dominant inheritance, characterized by motor disturbances, cognitive decline and behavioral and psychological symptoms. Since there is no cure, all treatment is aimed at improving quality of life. Music therapy is a non-pharmacological intervention, aiming to improve the quality of life, but its use and efficacy in patients with Huntington’s disease has hardly been studied.

In this article, a protocol is described to study the effects of music therapy in comparison with a control intervention to improve quality of life through stimulating expressive and communicative skills. By targeting these skills we assume that the social-cognitive functioning will improve, leading to a reduction in behavioral problems, resulting in an overall improvement of the quality of life in patients with Huntington’s disease.

**Methods/Design:**

The study is designed as a multi-center single-blind randomised controlled intervention trial. Sixty patients will be randomised using centre-stratified block-permuted randomisation. Patients will be recruited from four long-term care facilities specialized in Huntington’s disease-care in The Netherlands.

The outcome measure to assess changes in expressive and communication skills is the Behaviour Observation Scale Huntington and changes in behavior will be assessed by the Problem Behaviour Assesment-short version and by the BOSH. Measurements take place at baseline, then 8, 16 (end of intervention) and 12 weeks after the last intervention (follow-up).

**Discussion:**

This randomized controlled study will provide greater insight into the effectiveness of music therapy on activities of daily living, social-cognitive functioning and behavior problems by improving expressive and communication skills, thus leading to a better quality of life for patients with Huntington’s disease.

**Trial registration:**

Netherlands Trial Register: NTR4904, registration date Nov. 15, 2014.

## Background

Huntington’s Disease (HD) is a progressive, neurodegenerative disease with autosomal dominant inheritance, caused by an elongated CAG repeat on chromosome 4 [1]. HD is characterized by motor disturbances, cognitive decline and behavioral and psychosocial symptoms. The cognitive disorder in HD effects a broad variety of skills, including learning and memory, perceptual skills, executive efficiency and language [2]. Cognitive and behavioral changes are the most debilitating aspects of the disease and place the greatest burden on the patient as well as on their families and caregivers, and are often the main reason for institutionalization [3, 4]. Affective (mood) disorders (e.g. depression, anxiety, apathy, irritability) and behavioral problems (e.g. obsessive compulsive behavior and aggression) are frequent symptoms [5].

Verbal communication is often affected, due to motor impairment of speech. In addition, as a result of the cognitive decline, word retrieval is often impaired, although the knowledge of vocabulary is retained. As the disease progresses, the language content can no longer be processed properly and in the later stages of the disease, a patient with HD might not be able to communicate adequately [1].

As a result of the communication problems, patients are no longer able to express themselves. Revealing the patients’ unmet needs is, therefore, hindered and this might lead to irritability, impulsive and unwanted behavior (frequently signs in HD), causing much distress for patients and caregivers. Because of the behavioral symptoms, cognitive decline and the inability to express oneself, psychosocial problems develop [6]. Psychosocial stressors may include feelings of sadness and anxiety about the cognitive and physical decline, and about changes in social roles [7]. The gradual deterioration in communication skills, in combination with the behavioral problems in patients with HD, contributes to a decrease of functional health and a progressive inability to participate in various life situations, leading to loss of quality of life [8].

Since there is no cure for HD, the aim of all therapy, both pharmacological and non-pharmacological, is to improve quality of life [9]. One form of non-pharmacological intervention is music therapy.

Music therapy uses music experiences and patient-therapist relationships in order to effect therapeutic change [10]. Over the past decades, music therapy has been developed for patients with neurodegenerative diseases [11, 12]; its efficacy is shown in Table 1.

**Table 1 Tab1:** Benefits of music therapy for the neurodegenerative diseases

Benefits	Reference	Population
Improving and regulating emotional wellbeing	[13, 31]	Dementia, Huntington
Increasing social response	[13, 31]	Dementia, Huntington
Decreasing agitation	[13]	Dementia
Recalling life experiences	[14, 15, 31]	Dementia, Huntington
(re)establishing contact	[14, 15, 31]	Dementia, Huntington
Improving communication skills	[11, 12, 16, 31]	Dementia, Parkinson, Huntington, multiple disabilities
Reducing behavior and psychological symptoms	[17–20, 31]	Dementia
Improving gait	[9]	Parkinson

There is evidence that music therapy influences emotional well-being positively and that participation in music therapy increases social response in people with dementia [13]. It can decrease agitation and has a positive effect on enhancing communication and emotional well-being. Music therapy enables the recall of life experiences and the experience of pleasant emotions. Through music, contact can be established, especially as language deteriorates during the later stage of the dementing process [14, 15].

In a comprehensive literature search, Lee and McFerran [16] conclude that the non-verbal communication skills in individuals with profound and multiple disabilities improve as a result of song-choice during music therapy sessions. The results of their study support the belief that, through music therapy, the ability to express oneself will improve, contributing to improvement in the quality of life.

Furthermore, in a literature review, Patel et al. [17] demonstrate the effectiveness of MT in reducing behavioral and psychological symptoms of dementia. Several other meta-analyses and literature reviews have concluded that music therapy decreases symptoms related to behavioral problems in dementia [18–20].

On the basis of the above-mentioned literature, the assumption can be made that music therapy might be beneficial to patients with HD. Although knowledge on the use and efficacy of music therapy in HD is limited, it has been suggested that it can improve the communication skills of people with HD [21]. By improving the expressive and communication skills through music therapy (which will be assessed by the BOSH) we hypothesize that behavioral problems will decrease (assessed by the BOSH and the PBA-s), leading to an overall improvement of quality of life.

To test this hypothesis, we wrote a study protocol to answer the following questions:Does music therapy improve expressive and communicative skills in people with HD?Does music therapy reduce behavioral problems in patients with HD?Does music therapy improve the quality of life of patients with HD?

## Methods

### Study design

The study is a multi-centre, single-blind, randomised controlled intervention trial with two parallel arms. An overview of the study design is shown in a flow chart (see Fig. 1). It is single-blinded; the researcher who analyses all the scores is unaware of the allocation of the patients throughout the study. Also, the persons performing the baseline-assessments will be kept unaware of the allocation of the participants they are testing. Sixty patients (see sample size calculation below) will be randomised using centre-stratified, block-permuted randomisation following the procedure as described below. Two random groups will be created. The experimental group will be offered a music therapy program according to a structured protocol (see below), and the control group will participate in recreational day activities, following the same protocol as the experimental group. In addition, both groups will receive regular treatment (standard care, treatment as usual). Participants from both the experimental and the control groups will not be allowed to receive music therapy outside the study.

**Fig. 1 Fig1:**
[figure not shown]
Flowchart

### Procedure

#### Recruitment

Patients will be recruited from four long-term care facilities (nursing homes) in The Netherlands, all specialized in HD, with one or more units exclusively for HD-patients. Recruitment will be primarily done by the nursing staff and the responsible physician.

### Inclusion and exclusion criteria

Eligible patients must meet the following inclusion criteria:Age older than 18 yearsClinically and genetically confirmed Huntington’s Disease (CAG ≥ 36 repeats)Total Functional Capacity (TFC) ≤7

Exclusion criteria:patients who suffer from other neurological disorderspatients with poor comprehension of the Dutch languagepatients who have received music therapy in the past 3 monthspatients with a hearing impairment

Patients will be included irrespective of medication status and will be allowed to continue medication during the study. However, any change in medication should be avoided and carefully registered.

### Informed consent

Informed consent will be obtained by the nursing staff from patients who are cognitively able to understand the possible risks and benefits of the study. Proxy consent will be obtained from next of kin, or a legal guardian, if the patient is not able to give an informed consent.

### Baseline assessments

Clinical and demographic variables such as gender, age, (changes in) medication, number of CAG-repeats and (estimated) age at onset will be gathered for each participant. The stage of Huntington’s Disease will be assessed using the Total Functional Capacity (TFC) [22]. The TFC, part of the Unified Huntington Disease Rating Scale, consists of 13 points and contains 5 domains: work, finances, domestic chores, activities of daily living and care requirements [22]. As the disease progresses, the TFC-score will drop, giving clinicians a good indication about the functional stage of the disease. A score of 7 or lower indicates that the patient is in the mid/advanced stage, and so impaired in his functional capacities that assistance with self-care is needed [22]. Most of the patients that reside in the four long term care facilities that participate in the study have a TFC-score of 7 or lower. To ensure a homogeneous group, patients with a TFC score of > 7 will be excluded from participating in the research The TFC will be administered by the elderly care physician who is responsible for the patient.

The Mini Mental State Examination (MMSE) will be used to assess the cognitive function of the patients at baseline. A score of 23 or lower out of 30 indicates cognitive impairment [23]. The MMSE will be administered by the psychologist or the psychology assistant.

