### Randomisation

In order to minimize the impact of any between-center differences on the trial results, the participating centers will be stratified in the randomization process. Participants will be randomly assigned to either control or experimental group with a 1:1 allocation. To generate the random allocation sequence we use the method of center-stratified, block-permuted randomization [24]. The block size will vary. To diminish the chance of predictability, the date of signing the informed consent will determine the sequence in which the patients will be randomized. Not until all baseline measurements have been completed, the randomization code will be released to ensure allocation concealment.

Randomization will be conducted without any influence of the principal investigators, raters or therapists.

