### Statistical analysis

The primary outcome measures of this study are the differences in total and subscale-scores of the ADL and Social-Cognitive subscales of the BOSH and the PBA-s between groups (control versus MT) when baseline differences are taken into account.

Results will be analyzed on an intention-to-treat basis.

A mixed model analysis with repeated measures will be used to analyze the differential effects of music therapy versus recreational activities on the four GOSH and PBA-s scores (week 0, week 8 and week 16, and a follow-up score in week 28). The assessment number, ranging from one to four, will be used as the time variable of the repeated measures.

As stratified randomization often leads to correlation between treatment arms, it is necessary to adjust for the stratification factors in the analysis to obtain correct confidence intervals and p-values. By doing so, we maintain the type I error rate at its nominal level (usually set at 5 %), and avoid a reduction in power [30].

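### TFC ≤7 leaves disease stage varying among the 60 patients; naming baseline TFC as a covariate would be a free, small gain in precision

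*Protocol article*

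**What the plan says.** The eligibility list in Inclusion and exclusion criteria sets "Total Functional Capacity (TFC) ≤7" and gives no lower limit. Baseline assessments describes the scale as one that "consists of 13 points and contains 5 domains: work, finances, domestic chores, activities of daily living and care requirements", and places the admitted patients clinically: "A score of 7 or lower indicates that the patient is in the mid/advanced stage". It then remarks that "Most of the patients that reside in the four long term care facilities that participate in the study have a TFC-score of 7 or lower", and gives the purpose of the limit: "To ensure a homogeneous group, patients with a TFC score of > 7 will be excluded from participating in the research".

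In Randomisation, centre is the only stratification factor: "To generate the random allocation sequence we use the method of center-stratified, block-permuted randomization".

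Statistical analysis mentions two adjustments. The treatment comparison is made "between groups (control versus MT) when baseline differences are taken into account", without saying which baseline variables are meant. For the stratification factors it says that "it is necessary to adjust for the stratification factors in the analysis to obtain correct confidence intervals and p-values". The model is a repeated-measures mixed model whose four assessments include week 0. TFC is not mentioned in that section.

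**The concern.** The article counts on the entry limit to make patients alike, but the limit cannot do much of that work. It is open at the bottom, it spans two broad stages, and it turns away only a minority of the residents from whom patients are recruited. Informed consent points the same way: it provides both for patients who can consent themselves and for patients who need a proxy.

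Stage plausibly predicts the communication score and perhaps its course over 28 weeks. If it does so beyond what the week 0 score already tells us, leaving it out of the model costs some precision on the primary outcome and leaves chance differences in stage between the arms uncorrected. With 30 patients per arm, a covariate that every patient already has is worth using.

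**Working it through.** **1. What the limit admits.** The article gives 13 points and does not state the minimum. If the scale runs 0 to 13, scores 0 to 7 are 8 of 14 (57%). If it runs 1 to 13, scores 1 to 7 are 7 of 13 (54%). Either way more than half of the scale is admitted.

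**2. Chance imbalance in TFC.** Inputs: 30 per arm (Sample size). The article gives no TFC distribution, so the SD is assumed over a range. The upper end is a uniform spread over 0 to 7: SD = √((8² − 1)/12) = 2.29. The standard error of the arm difference in mean TFC is SD × √(2/30), and P(gap ≥ 1) = 2 × [1 − Φ(1/SE)].

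| Assumed TFC SD | SE | 95% limits of the gap | P(gap ≥ 1 point) |
|---|---|---|---|
| 1.0 | 0.26 | ±0.51 | < 0.1% |
| 1.5 | 0.39 | ±0.76 | 1% |
| 2.0 | 0.52 | ±1.01 | 5% |
| 2.29 | 0.59 | ±1.16 | 9% |

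**3. Precision gained by adding TFC to the baseline score.** Let r be the partial correlation of TFC with the follow-up score given the baseline score (assumed 0 to 0.4; the article gives none). Residual variance falls by r², and 60 adjusted patients are worth 60/(1 − r²) unadjusted for TFC.

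| r | Variance cut | 60/(1 − r²) |
|---|---|---|
| 0 | 0% | 60.0 |
| 0.2 | 4% | 62.5 |
| 0.3 | 9% | 65.9 |
| 0.4 | 16% | 71.4 |

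**4. The same gain as power.** The article's own figure is 30 per group for the Social-Cognitive subscale, from means 2.10 and 1.58 and SDs 0.79 and 0.75. With difference 0.52 and SD = √((0.79² + 0.75²)/2) = 0.770, the normal formula gives 28 per group one-sided and 35 two-sided at α 0.05 and 80% power. The article does not state sidedness. Taking 30 per group and a two-sided test, unadjusted power is Φ(0.52/(0.770 × √(2/30)) − 1.96) = Φ(0.655) = 74.4%.

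Replacing the SD by SD × √(1 − R²), where R² is the share of variance explained by the covariates:

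- Baseline score alone: 85.5% if it correlates 0.5 with follow-up, 95.6% if 0.7.
- Baseline score plus TFC, with TFC correlating 0.3 or 0.5 with follow-up and 0.3 to 0.7 with the baseline score: 85.7% to 91.5% in the first case, 95.6% to 98.2% in the second.

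TFC therefore adds about 0 to 6 percentage points of power once the baseline score is in the model. All these correlations are assumptions.

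**The case against.** The strongest case against raising this is that it corrects no error. A covariate list is commonly left to the analysis plan, which is not shown, and a condensed article need not give one. The reference to baseline differences is open and could already include TFC. Group homogeneity can also fairly be read as a shared need for help with self-care, which is how the article itself characterises scores of 7 or lower. The sample size does not rely on a narrower spread in TFC, since its SDs come from an earlier study with the BOSH. Most of this stands. It means that the absence of TFC is not a fault in itself and that the homogeneity sentence is at most loosely worded.

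A reader might go further and infer that stage is left uncontrolled, so that it remains in full as noise and imbalance. The document does not support that. The model includes week 0 and takes baseline differences into account, and a patient's week 0 BOSH score already carries much of the information on stage. Nor does it support the idea that TFC is collected and then ignored, because it decides eligibility and describes the sample.

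Two further inferences also fail. Chance imbalance after randomisation is not bias; the standard error allows for it. And stratifying 60 patients over four centres by centre alone is a defensible choice.

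What survives is narrower. The entry limit does not remove variation in stage, the text does not say whether TFC enters the model, and naming it in advance settles the matter at almost no cost.

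**Conclusion.** The point holds as a low-severity, free improvement. Stage will vary among the patients despite the entry limit, and the stated adjustment should absorb much, but not necessarily all, of its influence on the outcome.

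The document does not allow the remainder to be sized. The variance reduction of 0 to 16% rests on the assumed partial correlation of 0 to 0.4, and zero is a real possibility. The 9% chance of a gap of a full TFC point needs the widest assumed spread; at an SD of 1.5 it is about 1%. No conclusion of the trial is threatened, and rewording the homogeneity sentence would change no result.

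**What to change.** Keep the entry criterion and the centre stratification. In Statistical analysis, state that baseline TFC, as a continuous variable, is a prespecified covariate in the mixed model beside centre and the baseline score of the outcome being analysed. This also settles which variables the reference to baseline differences covers, before any data are seen.

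One detail should be fixed at the same time. If week 0 stays among the repeated responses instead of entering as a covariate, a TFC main effect shifts all four assessments alike and contributes little to the comparison of change. In that case TFC-by-assessment terms are needed as well (4 − 1 = 3 further terms).

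Cost: one sentence and 1 degree of freedom with the baseline score as covariate. In a single-time-point analysis of 60 patients, the intercept, treatment, three centre terms and the baseline score use 6 degrees of freedom; TFC takes the residual from 54 to 53. If TFC proves uninformative, that is all that is lost. No new data are needed, since TFC is measured on every patient at entry. Softening the homogeneity sentence, for example by saying that the limit restricts the trial to mid and advanced disease, is optional.

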### Randomisation

In order to minimize the impact of any between-center differences on the trial results, the participating centers will be stratified in the randomization process. Participants will be randomly assigned to either control or experimental group with a 1:1 allocation. To generate the random allocation sequence we use the method of center-stratified, block-permuted randomization [24]. The block size will vary. To diminish the chance of predictability, the date of signing the informed consent will determine the sequence in which the patients will be randomized. Not until all baseline measurements have been completed, the randomization code will be released to ensure allocation concealment.

Randomization will be conducted without any influence of the principal investigators, raters or therapists.

### Intervention

All participants (in both the experimental (intervention) group and the control group) will continue to receive treatment as usual. The intervention group will receive music therapy (MT-group). The control group will receive recreational therapy. The number of sessions (16) is equal in both groups, as are the day of the week and the time of the day at which the sessions will take place. Patients in both groups will participate in group interventions with three to five participants.

It must be noted that each of the four participating facilities have a different music therapist and recreational therapist attached to the research. However, all participating therapist have been instructed thoroughly to follow the same protocol. The reports that the therapist will fill out after each session will be used to monitor whether they have followed the instructions. See "compliance with treatment".

### Intervention group

The music therapists committed to the study are professionally trained and have been specifically informed about the clinical method and its theoretical basis.

The main goal of the music therapy intervention is to enhance communication skills by way of encouraging and stimulating the patients in interaction. The music therapy approach applied in this study is focused on encouraging and engaging patients in expressive musical interaction. The role of the therapist is to use musical parameters and interventions to stimulate expressive and communicative skills. The degree of verbal reflection may vary; the therapist will, however, encourage the participants to express themselves. The therapeutic process is based on the mutual construction of meaning of emerging thoughts, images, emotional content and expressive qualities that often originate from the musical experience [10].

A treatment guide specifies the procedures. It outlines the setting, goals and basic principles of the intervention; Table 1 (the benefits of music therapy for neurodegenerative diseases) is used as guideline. The available music therapy techniques to target the set goals are derived from the protocol “music therapy for Huntington’s patients on improving and stimulating communication and self-expression” [25]. However, the guidelines are to be administered flexibly according to the patient’s state of mind and his needs at that very moment. The clinical expertise of the therapist will be the guide, providing the therapist with enough “space” for flexible adaptation within the treatment guide. Also, the patients music preference, especially because most of the treatment involves receptive music therapy, is very important. This is the reason why the protocol allows and encourages the music therapist to adjust their treatment by way of “tailor made” sessions, providing each of the participants with his or her music preference.

The process used in each session is standard while the content is flexible. The intervention will be provided at the same time of the same day of the week by a formally trained, experienced music therapist. The sessions will take place once weekly with a total of 16 sessions, lasting 45 min. They will be standardized without limiting the music therapists in their interactions. The intervention itself, however, will be (partly) applied according to a protocol. Each session starts with the same welcome song/musical piece and ends with the same farewell song/musical piece. In doing so, the participants become familiar with the start and the end of each session. In between these two songs/musical pieces, the music therapist adjusts the level of each intervention to individual capacities. After the welcome song, the music therapy sessions may be varied: the music experiences can range from listening to music to playing or singing songs to free improvisation. therapist has the freedom to determine what works best at that very moment for that specific patient. The participants will listen to music selected, sung or played by the therapist. Active participation in music activities by singing or playing a musical instrument will be stimulated as much as possible. The music will be selected by the music therapist to incite expressive and communication skills and to reduce agitation, based on musical parameters, such as rhythm, melody, harmony, dynamics, timbre. After each song/musical intervention, the therapist will encourage and stimulate the participants to reflect verbally on the music [25].

Besides the music therapy intervention during the whole study, participants are not allowed to receive additional individual music therapy.

All participants are allowed to leave the session at all times.

